#### Secondary outcomes

2.7.2

Secondary outcomes include imaging parameters, functional assessments, and patient-reported clinical outcomes, which are used to comprehensively evaluate lumbar stability, pain, and functional status.

##### Imaging assessments

2.7.2.1

Magnetic resonance imaging (MRI) and X-ray examinations will be performed before and after the intervention to evaluate structural and functional changes of the lumbar spine. MRI scans will be conducted using a 3.0-T system to obtain axial T2-weighted images at the L4/5 level. The cross-sectional area (CSA), functional cross-sectional area (FCSA), and fatty infiltration of the lumbar multifidus muscles will be measured. Intervertebral disc degeneration will be assessed using the Pfirrmann grading system.

Standing flexion–extension lateral radiographs will be obtained to measure sagittal translation (ST), segmental angulation (SA), lumbosacral angle (LSA), and lumbar lordosis (Cobb angle from L1 to S1), which are used to evaluate lumbar stability. All imaging measurements will be performed independently by experienced radiologists and repeated three times, with the mean value recorded.

##### Pressure biofeedback unit (PBU) assessment

2.7.2.2

The pressure biofeedback unit (PBU) is used to assess deep core muscle function by monitoring pressure changes (37). Participants will perform standardized abdominal contraction tasks in the prone position. A mean pressure decrease of ≥ 4 mmHg across three trials will be considered indicative of effective transversus abdominis activation.

##### Patient-reported outcomes

2.7.2.3

Pain intensity will be assessed using the visual analog scale (VAS), ranging from 0 to 10, with higher scores indicating greater pain (38).

Functional disability will be evaluated using the Oswestry Disability Index (ODI), with scores ranging from 0% to 100%, where higher scores indicate greater disability (39).

Lumbar function will be assessed using the Japanese Orthopedic Association (JOA) score, with a maximum score of 29 and higher scores indicating better function (40).

Health-related quality of life will be evaluated using the 36-Item Short Form Health Survey (SF-36), with scores ranging from 0 to 100 for each domain and higher scores indicating better health status (41).

All outcome data will be recorded and verified by independent researchers. The collected data will be used for within-group comparisons before and after treatment, as well as between-group comparisons.Symptom recurrence will be defined as a clinically meaningful increase in pain intensity or functional disability compared with post-intervention levels, exceeding the minimal clinically important difference (MCID), where applicable.

#### Adverse events

2.7.3

All adverse events occurring during the intervention and follow-up period will be recorded and monitored, including but not limited to: increased local pain, muscle soreness, fatigue, skin abrasion or ecchymosis from Tuina, and exacerbation of radicular symptoms. Any discomfort or unexpected events will be documented in detail, including their type, severity, duration, and management. The relationship between adverse events and the intervention will be evaluated. Serious adverse events will be reported immediately to the ethics committee, and appropriate medical management will be provided. If necessary, the trial will be terminated to ensure participant safety.

### Quality control

2.8

#### Intervention delivery and fidelity

2.8.1

All interventions will be delivered by licensed practitioners with at least 3 years of clinical experience. Prior to trial initiation, all practitioners will undergo standardized training and pass a clinical trial operation assessment to ensure consistency in intervention delivery, including treatment intensity, frequency, and procedures according to the study protocol.

All Tuina treatments will be delivered by the same licensed Tuina practitioner, and all core stability training sessions will be supervised by the same licensed rehabilitation therapist throughout the study. Although therapist blinding is not feasible due to the nature of the interventions, therapists will strictly follow standardized treatment manuals and will not be involved in outcome assessment, data collection, or statistical analysis.

To ensure protocol adherence and minimize variability in treatment delivery, regular supervision sessions will be conducted throughout the study. Treatment fidelity will be monitored using a standardized checklist (Supplementary Table S2) and periodic supervision. In addition, a random sample of treatment sessions will be independently observed or recorded for fidelity evaluation. Adherence to the intervention protocol will also be documented throughout the study.

#### Outcome assessment

2.8.2

All outcome assessors will receive standardized training prior to study initiation to ensure consistency in data collection and scoring criteria. Whenever possible, assessments for the same participant will be conducted by the same assessor to minimize observer bias. Case report forms (CRFs) will be completed accurately and in full, without unauthorized modifications.

#### Participant management

2.8.3

Before the intervention, each participant will receive detailed instructions regarding the study procedures, precautions, and protocol requirements, and will be advised to refrain from using other interventions during the study period. Throughout the study, the research team will provide health consultation and monitoring. If pain or discomfort occurs during the intervention, participants will be instructed to promptly inform the research team, and appropriate medical management will be provided as necessary. Any adverse events or unexpected incidents will be recorded in detail, including their type, time of occurrence, severity, duration, and management measures.

### Data monitoring

2.9

Given the low-risk nature of the interventions in this study, no formal data monitoring committee (DMC) will be established. The study will be supervised by the research team of the Affiliated Rehabilitation Hospital of Fujian University of Traditional Chinese Medicine. All adverse events will be continuously monitored, recorded, and reviewed to ensure participant safety. Any serious adverse events will be reported promptly to the ethics committee, and appropriate measures will be taken if necessary.

### Data collection and management

2.10

A paper-based case report form (CRF) will be used for data collection. Outcome assessors will complete all CRFs in accordance with the study protocol, including treatment efficacy, adverse events, questionnaire data, musculoskeletal ultrasound results, and lumbar imaging findings. All data will be recorded accurately and comprehensively, with minimal corrections.The screening phase will last 1 week and will include the collection of baseline information, such as chief complaints, history of present illness, past medical history, family history, and routine physical examination findings. Any values outside clinically acceptable ranges will be reviewed and justified.All completed CRFs will be reviewed by designated research personnel before submission for data entry. Data will be entered into a Microsoft Excel database by two independent data managers who are not involved in the study, and double data entry and cross-checking will be performed to ensure accuracy and consistency with the original source documents. In case of discrepancies or uncertainties in the recorded data, queries will be resolved through consultation with the responsible investigators, and corrections will be made accordingly. After data verification, the final database will be confirmed and locked prior to statistical analysis. The study process will be supervised and audited by the Affiliated Rehabilitation Hospital of Fujian University of Traditional Chinese Medicine. All participant data will be kept confidential and will not be disclosed without permission.

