#### Objective outcomes

2.4.1

(Musculoskeletal ultrasound, MRI, X-ray, and pressure biofeedback unit) will be assessed by independent researchers who are blinded to group allocation and not involved in the intervention delivery.

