### Outcomes

2.7

The efficacy evaluation in this study will focus on the primary and secondary outcome measures assessed at baseline and immediately after the intervention. In addition, selected clinical outcomes, including pain intensity and functional status, will be reassessed at the 1-month follow-up using the VAS and ODI to evaluate the persistence of treatment effects. Follow-up assessments will be conducted by independent outcome assessors who are blinded to group allocation.All outcome assessments will be conducted by independent researchers who are blinded to group allocation and are not involved in other aspects of the study. The schedule of enrolment, interventions, and assessments is presented in (Figure 5).

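### Outcome assessors declared blinded are also assigned the adverse-event forms, which can show them that a participant received Tuina

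*Protocol article*

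**What the plan says.** All references are to the protocol article.

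- **Section 2.10 (Data collection and management)** names one role for the case report forms: "Outcome assessors will complete all CRFs in accordance with the study protocol, including treatment efficacy, adverse events, questionnaire data". Ultrasound results and lumbar imaging findings follow in the same list.
- **Section 2.7.3 (Adverse events)** lists the events to be recorded, among others "increased local pain, muscle soreness, fatigue, skin abrasion or ecchymosis from Tuina, and exacerbation of radicular symptoms". Type, severity, duration and management are to be documented. It adds "The relationship between adverse events and the intervention will be evaluated", without saying by whom.
- **Section 2.4.1 (Objective outcomes)** says that ultrasound, MRI, X-ray and pressure biofeedback "will be assessed by independent researchers who are blinded to group allocation and not involved in the intervention delivery". Section 2.4 states the blinding of assessors in general terms.
- **Section 2.7 (Outcomes)** describes all outcome assessors as "blinded to group allocation and are not involved in other aspects of the study".
- **Section 2.8.2 (Outcome assessment)** asks that, where possible, "assessments for the same participant will be conducted by the same assessor to minimize observer bias".
- **Section 2.8.1** keeps therapists out of data collection.
- **Section 2.7.1.1** has an experienced sonographer take the ultrasound measurements.

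**The concern.** Section 2.10 cannot be squared with 2.7. Recording adverse events is another aspect of the study, yet it is given to people said to have no other part in it. The task also carries information about treatment: a skin event attributed to Tuina can arise only in the two arms that receive Tuina.

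Participants and therapists are unblinded, so blinded assessment is the main protection for the objective outcomes. The Discussion counts it among the strengths and offers it as the mitigation for lack of blinding elsewhere. It also concedes that ultrasound depends on the operator, and the primary outcome, the transversus abdominis activation ratio, is an ultrasound measure. At stake is the credibility of that protection, chiefly in the comparison of the combination with core training alone. Unblinding that has already happened cannot be repaired in the analysis.

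**Working it through.** **1. Who could record adverse events, according to the text**

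| Role | What the protocol says |
|---|---|
| Outcome assessors | Complete all forms, adverse events included (2.10) |
| Therapists | Take no part in data collection (2.8.1) |
| Research team | Monitors participants, receives reports of discomfort and supervises the study (2.8.3, 2.9); no one named as completing the form |
| Sonographer | Takes the ultrasound measurements (2.7.1.1); no statement about adverse-event pages |

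Only 2.10 names a role for the forms. No section masks the adverse-event pages or separates them from the outcome pages.

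**2. What a Tuina skin event tells the assessor**

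| Arm | Receives Tuina | Can have such an event |
|---|---|---|
| Tuina | yes | yes |
| Core stability training | no | no |
| Combined | yes | yes |

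The event marks Tuina exposure, which 2 × 32 = 64 of the 96 participants share. It separates the combined and Tuina arms from core training alone. It does not separate Tuina alone from the combination.

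**3. When it can matter for the primary outcome**

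Ultrasound is done before and after the intervention. Only events recorded before the week-8 scan can influence that rating. Events first recorded during the 1-month follow-up cannot.

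**4. The reference effect**

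Section 2.5 plans on an effect size of 0.78, two-sided α 0.05 and power 0.80. A two-sample t-test calculation gives 26.8, rounded up to 27 per group (power 0.803 at 27). Allowing for 15% dropout, 27 / 0.85 = 31.8, so 32 per group and 96 in total. The stated figures reproduce, so 0.78 can be read as a difference in SD units between two arms.

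**5. Illustrative size of the bias**

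The protocol gives neither an event rate nor a size of rater bias. Both are assumed here:

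- p = share of a Tuina arm with a revealing event recorded before week 8: 5% to 20%, that is 32 × 0.05 = 1.6 to 32 × 0.20 = 6.4 participants per arm;
- s = shift in the rating of each such participant: 0.1 to 0.2 SD.

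Shift in the arm mean = p × s; relative to plan = p × s / 0.78.

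| p | s (SD) | Shift in arm mean (SD) | Share of 0.78 |
|---|---|---|---|
| 5% | 0.1 | 0.005 | 0.6% |
| 5% | 0.2 | 0.010 | 1.3% |
| 20% | 0.1 | 0.020 | 2.6% |
| 20% | 0.2 | 0.040 | 5.1% |

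These shifts apply to a comparison with core training alone. Between Tuina alone and the combination, equal event rates and equal shifts cancel, and the expected bias by this route is about zero.

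**The case against.** The strongest reply is that 2.10 condenses the division of labour. The sonographer measures, radiologists read the images, and the assessor may simply enter results that others produced. The research team already monitors safety, and delegation of individual forms is often left to a fuller document. The list in 2.7.3 is a list of events to watch for; no form page is shown. The judgement of causality is not assigned to assessors.

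Much of this stands, and it limits what can be said. A reader might infer three stronger things that the document does not support:

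- **That the forms reveal the arm.** They can reveal Tuina exposure, which two of the three arms share, and only for participants who have such an event.
- **That the person who rates the primary outcome is shown to fill in adverse-event pages.** Section 2.7.1.1 leaves open whether the sonographer sees them. Section 2.10 does place adverse events and ultrasound results with the same role, and 2.4.1 counts ultrasound among the blinded assessments.
- **That the bias could be 13–26% of the planned effect** (0.1 / 0.78 and 0.2 / 0.78). Those figures require every participant in the arm to be unblinded and shifted.

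The wish to keep the same assessor for a participant is also qualified as applying where possible, so it adds little.

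What the reply does not remove is the conflict in the text. The point does not rest on a detail left out: 2.10 positively assigns adverse events to assessors, against 2.4.1 and 2.7, and nothing in the article offsets it.

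**Conclusion.** The point holds as an internal contradiction with a plausible but limited route to unblinding. As written, assessors declared blinded record adverse events that can show Tuina exposure, for participants with such an event before the week-8 assessment. The threat is mainly to comparisons with core training alone. Under the assumed ranges (5–20% of a Tuina arm affected, 0.1–0.2 SD per affected rating) the arm mean moves by about 0.005–0.04 SD, roughly 0.6–5% of 0.78. The document supplies neither assumption, so this shows scale and is not an estimate. The likely bias is small. The change is still worth making, because it is cheap and protects the safeguard on which the objective outcomes rely.

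**What to change.** In section 2.10:

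- limit outcome assessors, including the sonographer, to the outcome pages;
- have existing research-team members who do not assess outcomes record adverse events and their relationship to the intervention;
- keep those pages from the assessors and the sonographer until that participant's outcome assessments are complete.

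Then reconcile the wording of 2.10 with 2.4.1 and 2.7, and name in 2.7.3 the role that judges the relationship to treatment.

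The cost is a protocol wording change, re-assignment of form pages among existing staff, and slightly more coordination at visits. The ultrasound measurement procedure need not change.

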### Statistical analysis

2.11

All statistical analyses will be performed using IBM SPSS Statistics (Version 27.0). Efficacy analyses will follow the intention-to-treat (ITT) principle, including all randomized participants. Continuous variables will be tested for normality and presented as mean ± standard deviation or median (interquartile range), as appropriate, while categorical variables will be expressed as counts and percentages. Baseline characteristics will be summarized descriptively without formal statistical comparisons. Primary and secondary outcomes will be analyzed using linear mixed-effects models, with group, time, and group-by-time interaction as fixed effects and subjects as random effects. Intervention duration (20 vs. 40 min) and baseline values of the outcome measures will be explicitly included as covariates to account for potential confounding effects. Therapist identity will be included as a random intercept to account for potential clustering effects. Model assumptions will be evaluated using residual diagnostics. If significant group-by-time interactions are detected, post-hoc pairwise comparisons with Bonferroni correction will be performed. Missing data will be handled using multiple imputation under the missing-at-random assumption. Safety analyses will include all participants who received at least one treatment, and adverse events will be compared using the chi-square test or Fisher's exact test, as appropriate. Sensitivity analyses, including complete-case analyses, per-protocol analyses, and analyses adjusted for intervention duration, will be conducted to assess the robustness of the primary outcome. All statistical tests will be two-sided, with a significance level set at *P* < 0.05, and 95% confidence intervals will be reported. Effect sizes (e.g., Cohen's d) will also be reported to facilitate interpretation of the clinical relevance of the findings.

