**Conclusion:**

This study is expected to provide high-quality evidence on the efficacy and safety of Tuina combined with core stability training in improving lumbar stability and clinical outcomes in patients with LDH.

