#### Primary outcome

2.7.1

The primary outcome is the muscle activation ratio of the transversus abdominis (TrA) assessed by musculoskeletal ultrasound, which reflects the neuromuscular control capacity of the deep core musculature. The muscle activation ratio is calculated as follows:

$$\begin{array}{l} \text{Activation ratio}=\frac{\text{muscle thickness duringcontraction}}{\text{muscle thickness at rest}} \end{array}$$

This measure has been widely used as an indicator of deep core muscle activation.

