## Discussion

3

To our knowledge, this study is among the first randomized controlled trials to investigate the combined effects of Tuina and core stability training in patients with lumbar disc herniation (LDH). Although both interventions are commonly used in clinical practice, high-quality evidence evaluating their combined efficacy remains limited. Given the high prevalence, prolonged disease course, and increasing trend toward younger onset of LDH, there is a need to explore effective and evidence-based rehabilitation strategies (25, 42). Tuina and core stability training may exert complementary effects, with Tuina primarily improving soft tissue mobility and pain, and core stability training enhancing neuromuscular control and spinal stability (18, 43). The combination may therefore provide complementary and potentially synergistic effects. This integrative approach may address both passive tissue dysfunction and active neuromuscular deficits.

This study has several strengths. It employs a randomized controlled design with blinded outcome assessment and data analysis to minimize potential bias. In addition, multiple outcome measures, including musculoskeletal ultrasound, lumbar imaging, and clinical assessments, are incorporated to comprehensively evaluate changes in lumbar stability and function. Importantly, this study focuses on lumbar stability as a core outcome, which has been insufficiently addressed in previous studies. In addition, the inclusion of a follow-up period allows for the assessment of short-term sustainability of treatment effects.

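### Every secondary outcome is tested at 0.05 with no error control across outcomes, yet the abstract promises high-quality efficacy evidence on clinical outcomes that are all secondary

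*Protocol article*

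**What the plan says.** Section 2.7.1 names one primary outcome: "The primary outcome is the muscle activation ratio of the transversus abdominis (TrA) assessed by musculoskeletal ultrasound". Section 2.5 bases the sample size on it alone.

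Section 2.11 gives the primary and the secondary outcomes one analysis: "Primary and secondary outcomes will be analyzed using linear mixed-effects models, with group, time, and group-by-time interaction as fixed effects". The threshold is common to all of them: "All statistical tests will be two-sided, with a significance level set at" P < 0.05. The only multiplicity step is this: "If significant group-by-time interactions are detected, post-hoc pairwise comparisons with Bonferroni correction will be performed". It corrects for the three group comparisons inside one outcome. Section 2.11 does not order the secondary outcomes, split alpha between them, or say that they are supportive or exploratory.

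The secondary outcomes are set out in section 2.7.2. For MRI, "The cross-sectional area (CSA), functional cross-sectional area (FCSA), and fatty infiltration of the lumbar multifidus muscles will be measured", and Pfirrmann grade is added. Four radiographic measures follow, "which are used to evaluate lumbar stability". Then come the pressure biofeedback unit (PBU), VAS, ODI, JOA and SF-36 scored by domain.

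The abstract's conclusion describes the trial as "expected to provide high-quality evidence on the efficacy and safety of Tuina combined with core stability training in improving lumbar stability and clinical outcomes". The Discussion adds: "Importantly, this study focuses on lumbar stability as a core outcome". Its limitations paragraph, by contrast, describes the expected evidence as preliminary.

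**The concern.** The promised conclusion reaches further than the error control. The abstract claims efficacy on two things, lumbar stability and clinical outcomes. Pain, disability, JOA score and quality of life are all secondary, and so are the four radiographs that the protocol itself assigns to stability. Each is tested at the same 0.05 as the primary, and nothing limits the chance of a false positive somewhere in the set.

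As written, the plan would let one significant result among many be reported as efficacy on stability or clinical benefit, even beside a negative primary. Nothing in section 2.11 tells the reader how much weight such a result may carry.

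**Working it through.** **The plan's own figure.** Section 2.5 gives d = 0.78, two-sided α = 0.05 and power 0.80. A two-sample t-test then needs 26.8, so 27 per group. Allowing for 15% dropout, 27 / 0.85 = 31.8, so 32 per group and 3 × 32 = 96. The stated size is reproduced. It is a calculation for the TrA ratio only; no error rate or power is stated for any secondary outcome.

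**Counting the secondary outcomes (section 2.7).**

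- MRI: CSA, FCSA, fatty infiltration, Pfirrmann = 4
- Radiographs: sagittal translation, segmental angulation, lumbosacral angle, lordosis = 4
- PBU = 1
- VAS, ODI, JOA = 3
- SF-36 = 1 if counted once, 8 if eight domains are assumed (the article scores it by domain but gives no number)

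This gives 4 + 4 + 1 + 3 + 1 = 13, or 4 + 4 + 1 + 3 + 8 = 20. Section 2.7.1.1 also measures external oblique, internal oblique and multifidus without labelling them primary or secondary; with these, 20 + 3 = 23. Separate tests of VAS and ODI at the 1-month follow-up would make 25.

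**Independent tests.** The chance of at least one significant interaction when no arm differs is 1 − 0.95^m:

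- m = 13: 1 − 0.95^13 = 48.7%
- m = 20: 1 − 0.95^20 = 64.2%
- m = 23: 1 − 0.95^23 = 69.3%

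**Correlated tests.** The outcomes overlap, so independence is an upper case. The article gives no correlations, so a range was assumed. The simulation used 20,000 null trials per setting, three arms of 27 and equally correlated normal outcomes. An omnibus F test at 0.05 stood in for the interaction test, followed by pairwise tests at 0.05/3 only if it was significant.

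| Outcomes | Correlation | Any significant interaction | Any Bonferroni-significant contrast favouring the combined arm |
|---|---|---|---|
| 13 | 0 | 49% | 18% |
| 13 | 0.5 | 35% | 12% |
| 13 | 0.8 | 20% | 7% |
| 20 | 0 | 65% | 27% |
| 20 | 0.5 | 43% | 15% |
| 20 | 0.8 | 24% | 8% |
| 1 | – | 5% | about 1.5% |

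With 23 outcomes the first column of results is 69%, 46% and 25%.

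A block structure may be more realistic: MRI, radiographs, PBU and patient-reported scales as blocks, with correlation 0.5 within and 0.1 between, and 32 per arm. It gives 54% and 20% for 20 outcomes, and 42% and 15% for 13.

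**Setting the claim against the outcomes.** The clinical-outcomes part of the abstract's claim is carried only by secondary outcomes. The stability part is carried partly by the radiographs, which are secondary, and partly by the primary: the Introduction links stability to neuromuscular function of the core muscles, and section 2.7.1 says the TrA ratio reflects that control.

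**The case against.** The strongest reply is that this is ordinary. One primary is named and powered, the rest are labelled secondary, and secondary outcomes are conventionally supportive. Ranking them is often left to a SAP, which is not shown. Section 2.11 directs its sensitivity analyses at the primary, and the Discussion calls for larger studies to confirm the findings. Much of this stands, and a missing hierarchy alone would not be a finding. What remains is a stated rule, 0.05 for all tests, next to a stated conclusion that the rule cannot support. The Discussion's caveat covers the study as a whole, restricts no outcome, and is at odds with the abstract's promise of high-quality evidence.

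A reader might go further and infer three things that the documents do not support.

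- **That the efficacy claim as a whole rests on the secondary outcomes.** It does not: the primary also bears on stability, and nothing says success may be declared on a secondary outcome alone.
- **That a chance positive is likely.** For any significant interaction this holds only near independence. For the result that would feed a false claim, a contrast favouring the combined arm, it holds in no setting tried: the highest figure for 20 outcomes is 27%.
- **That each outcome is judged at 0.05 with no correction.** This leaves out the Bonferroni step within an outcome, which brings a single outcome's chance of a false result favouring the combined arm down to about 1.5%.

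**Conclusion.** The point holds in a limited form. The abstract's conclusion extends to outcomes that are secondary, unpowered and without error control across the set. With 13 to 20 outcomes and correlations of 0 to 0.8, the chance of at least one false significant interaction is roughly 20% to 65%. The chance of at least one false contrast favouring the combined arm is roughly 7% to 27%, which is about 4 to 18 times the single-outcome rate of about 1.5%.

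These figures assume that no arm differs on any outcome, and they rest on the assumed SF-36 count and assumed correlations. They treat all outcomes as continuous, although Pfirrmann grade is ordinal and PBU may be read as a yes/no result, and they use an F test in place of the full mixed model. The exact size would change with these choices, but in every setting tried the chance is several times that for one outcome.

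**What to change.** - In section 2.11, state that confirmatory inference is limited to the TrA activation ratio. State also that secondary outcomes are supportive, reported as estimates with 95% confidence intervals and not as independent proof of efficacy.
- Reword the abstract's conclusion so that the efficacy claim refers to TrA activation, with stability and clinical outcomes as supporting evidence. Bring it into line with the Discussion's description of the evidence as preliminary.
- If the sponsor wants a confirmatory claim on a clinical or stability outcome, it should pre-specify its own short order, tested only after a positive primary and stopped at the first non-significant result. The documents give no basis for choosing that order on the sponsor's behalf.

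This needs wording changes only: no extra participants, visits or measurements. It should be done before any results are known, because a hierarchy declared afterwards carries little weight. The cost is that isolated significant secondary results can no longer be presented as proof of efficacy.

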#### Inclusion criteria

2.2.1

Diagnosis of lumbar disc herniation (LDH) according to established diagnostic criteria (25), confirmed by MRI showing disc protrusion, extrusion, or sequestration at L3/4, L4/5, or L5/S1 levels. Mild-to-moderate degenerative changes (Pfirrmann grade ≤ III) in the absence of significant nerve root compression do not exclude participation.Age ≥ 20 and ≤ 55 years, regardless of sex (3, 26).Duration of the disease ≥ 3 months (27, 28).Visual Analog Scale (VAS) score ≥ 3 and ≤ 6 (29).Provision of written informed consent, voluntary agreement to participate, and ability to comply with the treatment protocol.

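### Section 2.11 applies a linear mixed model to every secondary outcome, including the ordinal Pfirrmann grade, which read literally is also stored as a mean of three readings

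*Protocol article*

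**What the plan says.** Section 2.11 sets one model for all efficacy outcomes: "Primary and secondary outcomes will be analyzed using linear mixed-effects models", with fixed effects for group, time and their interaction. Baseline values enter as covariates, and 95% confidence intervals and effect sizes such as Cohen's d are to be reported. Categorical variables are mentioned only for description, as counts and percentages. Chi-square and Fisher tests are named only for adverse events. Residual diagnostics are planned, but no alternative model is named in case they fail.

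Section 2.7.2.1 lists the secondary imaging outcomes, taken before and after the intervention. Alongside the muscle areas and fatty infiltration it says: "Intervertebral disc degeneration will be assessed using the Pfirrmann grading system". The inclusion criteria (2.2.1) show that this is a class in Roman numerals: "Mild-to-moderate degenerative changes (Pfirrmann grade ≤ III". Section 2.7.2.1 ends: "All imaging measurements will be performed independently by experienced radiologists and repeated three times, with the mean value recorded".

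Section 2.7.2.2 describes the pressure biofeedback unit (PBU) as monitoring pressure changes and adds a threshold: "A mean pressure decrease of ≥ 4 mmHg across three trials will be considered indicative of effective transversus abdominis activation".

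**The concern.** A linear model treats the step from grade II to III as equal to the step from III to IV and estimates a difference in mean grade. The grades are ordered classes with no unit, so that difference, its confidence interval and a Cohen's d built on it have no clear meaning. Storing the mean of three readings makes this worse, because the recorded value need not be a grade at all.

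There is also a distributional question. If few patients change grade over 8 weeks, almost all changes from baseline are zero and the residuals are far from normal. The test may then not hold its nominal 5% level.

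What is at stake is one secondary outcome. It does have a role: section 3 presents lumbar imaging as a strength of the trial and counts MRI among the objective measures meant to offset the unblinded patient-reported outcomes.

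**Working it through.** **Which outcomes the rule fits**

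| Outcome | Scale in the article | Linear mixed model suitable? |
|---|---|---|
| Activation ratio (primary, 2.7.1) | continuous ratio | yes |
| Muscle areas, fatty infiltration, radiographic distances and angles (2.7.2.1) | continuous | yes |
| Pfirrmann grade (2.7.2.1) | ordinal class | no |
| PBU mean pressure change (2.7.2.2) | continuous, mmHg | yes |
| PBU at or above 4 mmHg, if analysed | binary | a binary model is the natural choice |

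**Averaging.** Readings II, II, III give (2 + 2 + 3)/3 = 2.33. Readings II, III, III give 2.67. Neither is a grade. The median of three readings is always a grade (here II and III).

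**Numbers of patients.** The article gives no figure for this outcome. From 2.5, 27 per group are required, and with 15% dropout 27/0.85 = 31.8, rounded up to 32. Three arms therefore hold 3 × 27 = 81 completers or 3 × 32 = 96 randomized.

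**Chance that nobody changes grade.** Let p be the share of patients who change grade. The documents give no value, so 2%, 5% and 10% are assumed. The chance that none of N patients changes is (1 − p)^N.

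| p | All three arms, N = 81 | Two arms only, N = 54 |
|---|---|---|
| 2% | 0.98^81 = 19% | 0.98^54 = 34% |
| 5% | 0.95^81 = 1.6% | 0.95^54 = 6% |
| 10% | 0.90^81 = 0.02% | 0.90^54 = 0.3% |

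The three-arm column is the relevant one, because 2.11 fits one model to all arms.

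**Error rate under the null.** Simulation with 32 per arm, three arms, no true effect and 2,000 runs per row. Assumed baseline grades were II to V with probabilities 0.2, 0.4, 0.3 and 0.1. Changes were one whole grade, equally likely up or down. The analysis was a baseline-adjusted linear model with an F test for group at 5%. It is simpler than the full mixed model. Runs with no residual variance counted as no rejection.

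| p | Rejection rate | Median residual excess kurtosis |
|---|---|---|
| 2% | 0.0075 | not computable |
| 5% | 0.0325 | 17.5 |
| 10% | 0.052 | 7.1 |
| 30% | 0.040 | 0.4 |

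The simulation error near 5% is √(0.05 × 0.95/2000) = 0.005, so the last two rows are close to nominal. A two-arm t-test on changes of −1, 0 or +1 with 27 per arm behaves similarly, rejecting in 0.3%, 2.6% and 4.6% of runs at p = 2%, 5% and 10%.

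**PBU, in case pass/fail were analysed.** With 32 per arm, two arms and pass rates from 0.5 to 0.95, a t-test on the 0/1 result rejects under the null in about 3% to 6% of runs. For 0.6 against 0.9 its power is 0.835, the same as a likelihood-ratio test on the 2×2 table.

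**The case against.** Several objections carry weight.

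- **PBU.** A reader might infer from the 4 mmHg rule that the PBU is a pass/fail endpoint and that the linear model is wrong for it. The text does not support this. It describes a mean pressure decrease, which is continuous, and offers the threshold as an aid to interpretation. Nothing makes pass/fail the analysed variable. This objection stands.
- **Averaging.** The article measures areas, distances and angles but assesses degeneration by grade, and the averaging sentence closes the paragraph on radiographs. It may have been meant only for the quantitative measures. That reading is fair, so the averaging is a literal reading and not an established intention. The wording still covers all imaging measurements.
- **False positives and lack of variance.** A reader might infer inflated false positives or a model that often cannot be fitted. Neither is shown. The rejection rates are at or below about 5%. The no-change scenario is material only at the lowest assumed rate, and averaged readings would add fractional variation that makes it less likely. If nobody changes, a proportional-odds model cannot estimate an effect either.
- **Mean grades are common, and an analysis plan may exist.** A mean difference in a graded score is a familiar if imperfect summary, and a condensed article may leave outcome-specific models to a plan that is not shown. The point, however, does not rest on missing detail. The article states a rule, and that rule covers an outcome it does not fit. Counts and percentages are offered only for description, and the residual diagnostics lead to no stated alternative.

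**Conclusion.** The concern holds for the Pfirrmann grade only. As written, 2.11 yields a mean-grade difference, confidence interval and Cohen's d that do not suit an ordinal scale. A literal reading of 2.7.2.1 adds recorded values that are not grades.

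The harm is mainly one of interpretation. Calibration suffers only if change is rare: about 1% rejection under the null at 2% change, 3% at 5% and 5% at 10%. These figures rest on assumed change rates, assumed baseline grades, whole-grade readings and a simplified linear model. They point to a conservative test, with no inflation of false positives.

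Severity is minor. One secondary outcome is affected. The primary outcome and the sample size are not.

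**What to change.** 1. In 2.11, limit the linear mixed model sentence to continuous outcomes.
2. In 2.7.2.1, limit the averaging sentence to quantitative imaging measures. For the Pfirrmann grade, record an agreed, median or modal grade. A rule is needed for three different readings if the mode is chosen; the median avoids this.
3. In 2.11, analyse the post-treatment grade with a proportional-odds model adjusted for baseline grade. If few patients change, report counts improved, unchanged and worsened by arm with an exact test.
4. In 2.7.2.2, state that the analysed PBU variable is the mean pressure change in mmHg, under the linear model. Only if the 4 mmHg result is also analysed, add a binary model such as logistic regression with a risk difference.

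The cost is a few lines in three sections. No new data are needed and the methods are standard. The recording change is best made before readings are averaged onto the case report forms, and the analysis change before the database is locked.
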